### Outcomes

The primary outcome is the proportion of children diagnosed with TB defined as the number of pediatric TB cases diagnosed over the number of children attending the child healthcare services during the study period.

Main secondary outcomes include:
Proportion of children screened for TB among the total number of children attending the child healthcare services.Proportion of children diagnosed with TB (bacteriologically or clinically) among presumptive TB cases, overall and disaggregated by HIV status and nutrition status.Time from screening to clinical or bacteriologic diagnosis.Time from diagnosis to treatment initiation.Proportion of cases with a bacteriologically confirmed diagnosis.Treatment outcomes for patients initiated on treatment according to WHO categories, with a focus on treatment completion rate.Cost-effectiveness from a health system perspective, as US dollars per disability-adjusted life-year (DALY) averted.Comprehensive understanding of caregivers’ perceptions and patients’ and communities’ acceptability of receiving integrated pediatric TB services within pediatric care.

### Adverse events

Parents/caregivers are informed of any side effect which could be associated with TB diagnosis procedures, especially invasive sample collections (gastric aspirate, lymph node fine needle aspiration, CSF collection, ascites collection, nasopharyngeal aspirate), and with TB treatment.

The investigators describe adverse events occurring during follow-up of children in a specific section of the case report form.

Serious adverse events as defined by ICH [25] or unexpected adverse events are reported to the ethics committees as per their guidance.

Since drugs dispensed during the study are part of national standard of care, children who develop adverse reactions are managed according to national standard of care, according to the national pediatric TB guidelines in Kenya and ad-hoc guidelines in Cameroon. The study nurse collects outcome data from clinical and laboratory reports.

### Risks and benefits for participants

Patients who utilize CaP TB supported facilities in the intervention phase benefit from better access to TB services as part of the general CaP TB program implementation. There is no additional benefit to study participants.

Risks to all participants is minimal. Potential risks include the potential for unintended disclosure of mother/caregiver and infant’s TB infection status and for those who are HIV infected their HIV status.

Children enrolled in the INPUT study are identified by their unique study identifier, and data collection and forms are linked to the patient using this unique identifier only. All study documents are maintained by the study team in a locked cabinet in an office with limited access. Following study completion and all analyses, paper-based study documents for all data collection activities will be destroyed after 7 years.

Caregivers may also feel discomfort in answering some of the interview questions such as those to child’s exposure to TB infection at home. Interviews are conducted in private areas free from general view and out of hearing reach. Study staff is thoroughly trained on interviewing techniques in general and those related to this study in particular.

### Sample size

The total number of clusters enrolled in this study has been determined under three assumptions: 1) the expected “sample size” of clusters, which is the number of children seen per month in each cluster; 2) the expected baseline “detection rate”, which is the proportion of cases diagnosed on the total number of children, during the standard-of-care phase; and 3) the “effect size” of the intervention which is the expected increase in detection rate between standard-of-care and intervention phase. According to baseline records, we estimate that the number of consultations in children less than 5 years of age will be at least 500 per month in each cluster. We assume that at least 2 children will be diagnosed with TB per 1000 children attending the child health care services, under standard-of-care. Published studies on interventions to enhance case detection in adults demonstrated an effect of the intervention of 50% [15]. However, it is well known that under-reporting of child TB cases is much more prevalent than adult TB cases [2], and thus we believe it will be more subject to improvement. Indeed, whereas the incidence of TB in children is expected to be 10 to 12% of the total number of TB cases in a particular country, the notified TB cases in children represents only 6% of the total number of TB cases in Cameroon and Kenya. We designed the study according to an expected effect size ranging between 50 and 100%.

Based on a stepped-wedge design, with 2000 children attending consultations during each four-month step of the study, four randomly selected study sites per step and 12 sites in total (three steps in the study), and an ICC correlation of 0.001, we will have 96.5% power to see a doubling in the case detection from two to four per 1000.

With this design and assumptions, we expect to follow 300 confirmed pediatric TB cases during the whole study duration. Current TB treatment completion rates in routine care are estimated at least at 70%. With 96 cases expected under standard-of-care and 192 cases under intervention, the power will be 80% to detect a 20% increase in completion rate.

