### Randomization and blinding

The randomization sequence was generated by the study biostatistician using Stata 15.0 statistical software, with stratification by country. In each country, two sites were allocated to cross into the intervention after 4 months under standard-of-care phase, 2 after 8 months under standard-of-care, and 2 after 12 months under standard-of-care. The allocation sequence remains concealed from all investigators during the first 3 months of the study, so that all sites start under standard-of-care blinded of when the intervention phase will start. Then, the biostatistician discloses to Principal Investigators which four sites in the two countries have been randomized to start the intervention in the first step (see Fig. 2). The four sites undergo a transition phase of 1 month with trainings before crossing to the intervention phase. All other sites continue in the standard-of-care, still blinded on the time when they will start the intervention, until the last month before the next step. The one-month notice given before starting into the transition phase will allow sites to adequately plan for trainings in the study sites.

The study design does not allow the site investigators to be blinded after assignment to interventions.

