### Statistical considerations

In a stepped wedge study, exposed (intervention) and unexposed (standard-of-care) observation periods take the place of “arms” in parallel cluster trials. Thus, the distribution of outcomes across unexposed observation periods is compared with that across the exposed observation periods [20, 21].

Characteristics of the individuals and clusters will be summarized by exposure status (intervention versus standard-of-care period) to assess for potential selection biases and lack of balance. These characteristics will also be compared by steps. This will include the numbers analyzed, the average cluster size, cluster characteristics (in terms of TB care cascade), and important patient characteristics (TB treatment outcomes). All comparisons will be performed with a level of significance alpha of 5%.

Following an intention to treat principle, clusters will be analyzed according to their randomized crossover time irrespective of whether crossover was achieved at the desired time. In addition, we will carry on per protocol analyzes where the clusters will be analyzed according to the real timing on which the crossover actually occurred.

Data collected during the one-month transition phase from standard-of-care to intervention will not be considered in the analysis of outcomes, in order to minimize contamination between study periods.

We will estimate the TB detection rates for each cluster during each step. We will then summarize the detection rates by intervention period (standard-of-care versus integration) and display the summaries using graphs. To estimate the effect of integration on TB detection rates (i.e., proportion of cases diagnosed), we will use generalized linear mixed Poisson models. The effect will be presented as rate ratio and associated 95% confidence interval.

We will use time to event survival analysis approaches with frailties to estimate the effect of the intervention on treatment completion. This approach allows us to account for TB patients lost to follow-up or who transfer to other facilities while estimating treatment completion rates. In addition, we will use descriptive analysis to assess the fidelity of the implementation of the intervention over time and secondary outcomes that are likely to be infrequent and thus with limited power to detect differences.

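### The stated 96.5% power for the primary outcome is too high for the protocol's own inputs: it is about 87%, and about 83% once the excluded transition month is taken out

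*Protocol article*

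**What the plan says.** The Sample size section of the protocol article assumes that consultations in children under 5 "will be at least 500 per month in each cluster", hence a calculation "with 2000 children attending consultations during each four-month step of the study". There are 12 sites, four crossing at each of three steps. The baseline is given as: "We assume that at least 2 children will be diagnosed with TB per 1000 children attending the child health care services, under standard-of-care". The power statement is "an ICC correlation of 0.001, we will have 96.5% power to see a doubling in the case detection from two to four per 1000". The same section expects 96 cases under standard of care and 192 under intervention.

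Randomization and blinding puts the crossovers after 4, 8 and 12 months and adds: "The four sites undergo a transition phase of 1 month with trainings before crossing to the intervention phase". Statistical considerations sets alpha at 5%, plans a mixed Poisson model with a rate ratio and 95% confidence interval, and states: "Data collected during the one-month transition phase from standard-of-care to intervention will not be considered in the analysis of outcomes".

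**The concern.** Two features of the planned trial appear to be missing from the power figure.

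1. **Variance.** For a rare binary outcome the variance is nearly proportional to the rate, so a doubling of detection doubles the variance in the intervention periods. A calculation that keeps the 2 per 1000 variance everywhere understates the standard error. The planned Poisson model has the same property: its variance rises with the rate.
2. **Excluded month.** The 96 and 192 expected cases correspond to full cells of 2000 children, but one month per cluster does not enter the outcome analysis. That month lies beside the crossover, where a stepped-wedge comparison draws most of its information.

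This is the only power figure for the primary outcome. The Discussion already calls the case estimate optimistic and warns of low power if cases are fewer. A reader who sees 96.5% will believe there is ample reserve against that shortfall.

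**Working it through.** **Inputs from the protocol article.** I = 12 clusters; crossovers at 4, 8 and 12 months, so T = 4 periods of four months; m = 2000 children per cell (500 × 4); ICC ρ = 0.001; rates 0.002 and 0.004, difference δ = 0.002; alpha 5%. Two-sided testing is assumed, as sidedness is not stated.

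**Check of the grid.** There are 24 standard-of-care and 24 intervention cells. 24 × 2000 × 0.002 = 96 and 24 × 2000 × 0.004 = 192, which are the protocol's own case counts.

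**Formula (Hussey–Hughes: random cluster intercept, fixed period effects).**

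Var = I σ² (σ² + T τ²) / [(IU − W) σ² + (U² + ITU − TW − IV) τ²]

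Here τ² = ρ × total variance and σ² = (1 − ρ) × total variance / m.

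- U = number of intervention cells = 24
- W = 0² + 4² + 8² + 12² = 224
- V = 4 × (3² + 2² + 1²) = 56
- IU − W = 288 − 224 = 64
- U² + ITU − TW − IV = 576 + 1152 − 896 − 672 = 160

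**Step 1: reproduce the stated figure.** Total variance 0.002 × 0.998 = 0.001996 in every cell.

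- τ² = 1.996e-6; σ² = 9.97e-7
- Var = 12 × 9.97e-7 × 8.981e-6 / (64 × 9.97e-7 + 160 × 1.996e-6) = 2.804e-7, so SE = 5.295e-4
- z = 0.002 / 5.295e-4 = 3.777; power = Φ(3.777 − 1.960) = **96.5%**

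**Step 2: use the planned rates.** The intervention variance is 0.004 × 0.996 = 0.003984. The average over the two halves of the grid is (0.001996 + 0.003984) / 2 = 0.00299.

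- SE = 5.295e-4 × √(0.00299 / 0.001996) = 6.481e-4
- z = 3.086; power = Φ(1.126) = **87.0%**

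**Step 3: remove the transition month.** One cell per cluster drops from 2000 to 1500 children. With unequal cells the closed formula no longer applies, so the same model was solved by generalized least squares.

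- SE = 6.871e-4; z = 2.911; power = Φ(0.951) = **82.9%**
- With a common variance, the result is the same whether the month comes out of the last standard-of-care cell or the first intervention cell.

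**Step 4: other variants.**

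| Variance used | Full cells | Transition month removed |
|---|---|---|
| 2 per 1000 in every cell | 96.5% | 94.5% |
| Average of the two variances | 87.0% | 82.9% |
| Cell-specific binomial variances | 87.8–88.9% | 83.5–85.6% |
| Log-scale Poisson mixed model | 86.5–87.6% | 82.0–84.1% |
| Simulated Poisson random-intercept model (3000 runs) | 85.9% | 80.7% |

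The ranges reflect which rate fixes the between-cluster variance and which cell loses the month. The first row shows that most of the drop comes from the variance; removing the month alone costs about two points.

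**Sensitivity, not in the protocol.** If a cluster's level is correlated 0.9 rather than 1 between periods (an assumption), the average-variance figures fall to 81.1% with full cells and 77.2% with the month removed.

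**The case against.** - **The cause is inferred.** The protocol names no formula or variance, and the match is not unique: the average variance with an ICC of 0 also gives 96.5% (SE 5.294e-4). This stands as a caveat on how the figure arose. It does not rescue the figure, because the protocol states an ICC of 0.001.
- **The 83% depends on where the transition month falls.** If it were added to the four-month steps, no cell would lose children and about 87% would stand. Enrolment from May 2019 to October 2020 spans 18 months against 16 in the grid, and the wording on one month's notice before the transition can be read that way. However, allocation is concealed for three months, a one-month transition follows, and crossover comes at month 4. Later crossovers at 8 and 12 months leave no spare month. Inside the grid is the better reading, though Figure 1, which might settle it, was not available.
- **An averaged variance is itself an approximation.** Cell-specific variances give one to two points more with full cells. The planned Poisson model gives nearly the same as the average, so 87% and 83% are fair central values within a range.
- **The design survives.** Power for a doubling stays above 80% under the stated inputs, and the children per month and baseline rate are given as minimums. This limits the consequence but does not make 96.5% correct for the inputs beside it.

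**Conclusion.** The concern holds. At the stated ICC, cell size and rates, power to detect a doubling is about 87% (86.5% to 88.9% across analytic variants), not 96.5%. After the month that the analysis excludes, it is about 83% (82.0% to 85.6%; 80.7% by simulation). The chance of missing a true doubling rises from 3.5% to 13% or 17%, about four to five times the stated risk (13.0 / 3.5 = 3.7; 17.1 / 3.5 = 4.9).

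These figures assume two-sided 5% testing, fixed period effects and no cluster-by-period variation. The second figure also assumes that the transition month lies inside the four-month steps. They allow for no shortfall in cases and no small-sample correction for 12 clusters. The error is an overstated power figure, not a design that fails at the planned effect.

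**What to change.** In the Sample size section, replace 96.5% with about 87%, or with about 83% if the power is to describe the data actually analysed. Recompute with the intervention-period variance in the intervention cells, and with 1500 instead of 2000 children in the cell that loses the transition month. Name the formula and the variance used. State that the result assumes an ICC of 0.001 and no cluster-by-period variation, and say whether the transition month lies within the four-month step.

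The cost is one rewritten power statement and a less favourable number. No sites, children or procedures change.

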### Study design

We are conducting a multi-country stepped-wedge cluster-randomized controlled trial to compare two strategies for case detection and management of tuberculosis in children under the age of 5 years: i) The standard of care offers pediatric TB services based on current routine approach (national standard of care); ii) The CaP TB intervention will offer pediatric TB services integrated into key child healthcare services.

In this study, a stepped wedge design [20] has been preferred to parallel cluster trial for the following reasons: It allows every site participating in the study to eventually be exposed to the CaP TB intervention, which is in line with the scale up of CaP TB activities, and more acceptable for the MoHs. The phased roll-out of CaP TB activities provides logistical advantages. The intra-cluster correlation is anticipated to be high and cluster size large so that a stepped wedge design is likely to be more efficient than the simple parallel cluster design [21], and will require a smaller number of clusters [22]. Finally, stepped-wedge design allows for the control of trends over time due to external changes in the way care is delivered, for example changes in national guidelines.

In INPUT study, the randomization unit or cluster is defined as a district or sub-district hospital (the hub) and some of its attached primary health care centers (spokes) that refer patients or samples to these facilities for TB diagnosis. A randomization list prepared by the biostatistician in EGPAF determines time of enrollment of each of these sites into the intervention phase.

Figure 1 shows the stepped wedge study design. Justification for total number of steps, number of clusters per step and duration of steps is given in the “sample size” section.

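### The 80% power for treatment completion has no stated scale, method or ICC, and the calculation that reproduces the primary outcome's 96.5% does not support it on either reading of the 20% increase

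*Protocol article*

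**What the plan says.** All the figures are in the protocol article, Sample size section. For case detection, the section names the stepped-wedge design, 12 sites, three steps, 2000 children per four-month step and "an ICC correlation of 0.001, we will have 96.5% power to see a doubling" from two to four per 1000.

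The next paragraph turns to completion. It says "we expect to follow 300 confirmed pediatric TB cases during the whole study duration", that "Current TB treatment completion rates in routine care are estimated at least at 70" per cent, and then "With 96 cases expected under standard-of-care and 192 cases under intervention, the power will be 80% to detect a 20% increase in completion rate". It gives no ICC for completion, no formula, and no indication of whether the 20% is a ratio or a difference in percentage points.

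The Study design section gives as one reason for the design that a "stepped-wedge design allows for the control of trends over time due to external changes in the way care is delivered". The Statistical considerations section plans survival models with frailties for completion and sets the significance level at 5%, without saying one- or two-sided.

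**The concern.** The two power statements stand side by side but need not share a basis. The first is explicitly a stepped-wedge figure. The second is worded as a comparison of two totals, 96 and 192.

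In this design exposure rises with calendar time: 0, 1/3, 2/3 and all of the clusters are exposed in the four steps. A calculation that treats the two totals as parallel samples leaves out the step adjustment and therefore overstates the information about the intervention effect.

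Improved treatment outcomes are part of the hypothesis, and completion is the only secondary outcome with a power statement. If the 80% is too high, a non-significant completion result could be given more weight than it deserves. The limitations in the Discussion warn of low power only if fewer cases are found than expected, not at the planned numbers.

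**Working it through.** **Inputs.** From Sample size: baseline 70%; 96 and 192 cases; 12 clusters; 2000 children per cluster-step; 2 and 4 cases per 1000. From Randomization and blinding: crossover after 4, 8 and 12 months, so four steps and three sequences of four clusters. Standard-of-care cells: 4 × (1+2+3) = 24; intervention cells: 4 × (3+2+1) = 24. Cases per cell: 2000 × 0.002 = 4 and 2000 × 0.004 = 8. This returns the protocol's counts: 24 × 4 = 96 and 24 × 8 = 192. *Assumed:* two-sided 5%; ICC for completion 0 to 0.10.

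**Step 1. Two independent groups.** Power = Φ[(d − 1.96·s0)/s1], with s0 the pooled and s1 the unpooled standard error.

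- 70% to 84%, 96/192: pooled p = (67.2 + 161.28)/288 = 0.7933; s0 = 0.0506; s1 = √(0.21/96 + 0.1344/192) = 0.0537. Power = Φ[(0.14 − 0.0992)/0.0537] = Φ(0.76) = **77.6%** (74.1% with s1 throughout).
- 70% to 84%, 100/200 (the rounded 300 cases): **79.2%**.
- 70% to 90%, 96/192: **98%**.

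So 80% is close to the relative reading without any design adjustment.

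**Step 2. The primary figure, to identify the protocol's method.** For cluster i, the design matrix Z_i holds the exposure indicator (effect θ) and four step indicators. The covariance of the cell means is V_i = diag(v/n) + τ²J, with v the binomial variance and τ² = ICC/(1−ICC) × v. Var(θ̂) is the θ element of (Σ Z_i′V_i⁻¹Z_i)⁻¹, and power = Φ(d/SE − 1.96). For 0.002 to 0.004, n = 2000 and ICC 0.001:

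- v at the control rate: SE 0.00053, power = Φ(3.775 − 1.96) = **96.5%**, the stated figure.
- Average or pooled v: 87%. Arm-specific v: 89%.
- Without step effects: above 99.9% under every convention.

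The stated 96.5% is therefore matched by step effects with control-rate variance.

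**Step 3. The same calculation for completion, 4 and 8 cases per cell.** Power in %:

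| Effect | Variance | ICC 0 | 0.001 | 0.01 | 0.05 | 0.10 |
|---|---|---|---|---|---|---|
| 70→84 | control-rate | 37.4 | 37.2 | 35.3 | 31.3 | 29.4 |
| 70→84 | arm-specific | 42.2 | 41.9 | 39.7 | 35.4 | 33.6 |
| 70→84 | average | 44.1 | 43.8 | 41.7 | 37.0 | 34.7 |
| 70→84 | pooled (1:2) | 45.8 | 45.5 | 43.4 | 38.5 | 36.1 |
| 70→90 | control-rate | 64.9 | 64.5 | 61.9 | 55.8 | 52.6 |
| 70→90 | arm-specific | 75.5 | 75.0 | 72.1 | 67.0 | 64.9 |
| 70→90 | average | 79.1 | 78.8 | 76.3 | 70.2 | 66.9 |
| 70→90 | pooled (1:2) | 82.1 | 81.8 | 79.5 | 73.5 | 70.2 |

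Worked row, control-rate, ICC 0.001: SE = 0.0857. Relative: 0.14/0.0857 − 1.96 = −0.33, Φ = 37%. Absolute: 0.20/0.0857 − 1.96 = 0.37, Φ ≈ 65%.

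Holding total variance fixed instead (τ² = ICC × v) leaves the ICC 0.001 column practically unchanged and raises the ICC 0.10 column by up to about 5 points.

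**Step 4. Where the loss arises.** With arm-specific variance and ICC 0, SE is 0.0537 without step effects and 0.0794 with them: variance × (0.0794/0.0537)² = 2.2. For 70% to 84% with cluster effects but no step effects, power over ICC 0-0.10 stays at 64-79%. Most of the loss is therefore due to the step adjustment rather than the assumed ICC.

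**Cross-check.** A simulated logistic model with step effects and no cluster variance gave 47% (84%) and 79% (90%).

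**The case against.** A reader might infer that the 80% was certainly computed from a two-group formula and that the true power is one narrow figure near 40%. The documents do not support either inference.

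- **No formula is named.** The two-group origin is an inference, and on exactly 96/192 that formula gives 77.6%, not 80%.
- **The absolute reading is open.** For 70% to 90% at ICC 0.001, the only ICC in the document, a stepped-wedge calculation gives 79-82% with average or pooled variance. If that was the basis, the 80% already reflects the design. This stands as a possibility. It requires a different variance convention from the one that matches the 96.5% one paragraph earlier, and an ICC set for an outcome of 2 per 1000 to carry over to one of 70%. The other effect sizes in the section (50%, 50 to 100%, a doubling) are relative, which favours the relative reading without settling it.
- **The completion ICC is not in the document.** Agreed; hence the range. On the relative reading the shortfall remains at ICC 0.
- **Model terms may be left to the analysis plan.** Agreed: the lack of a named step term is not in itself a fault. The point concerns a printed power figure.
- **Completion is secondary.** Agreed. The number of clusters rests on case detection, and no passage says that a null completion result would be read as no benefit.

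**Conclusion.** The point holds in conditional form. The 80% cannot be interpreted as written, because the scale of the 20%, the method and the completion ICC are all missing.

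- Relative reading (the likelier one): about 37-46% at ICC 0-0.001 and 29-43% at ICC 0.01-0.10.
- Absolute reading: about 65-82% at ICC 0.001 and 53-74% at ICC 0.05-0.10. Here 80% is reachable under some variance conventions at a very small ICC.
- With the convention that reproduces the protocol's own 96.5%, at ICC 0.001: 37% or 65%. Neither is 80%.

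This rests on 4 and 8 cases per cell as planned, a two-sided 5% test, step effects, a cluster effect constant over time, an assumed completion ICC, and a comparison of proportions standing in for the planned frailty survival model. It does not affect the primary power figure, which reproduces.

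**What to change.** In Sample size:

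1. State whether the 20% is relative or absolute. Only the sponsor can say which was meant.
2. Recalculate completion power by the stepped-wedge method used for the primary outcome, with step effects and a stated ICC for completion, shown over a range.
3. Replace the 80% with the result.

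In the analysis of completion, adjust the frailty model for step, as the design's claim to control time trends requires. If the analysis plan already does so, only the power statement changes. If the recalculated power is well below 80%, present completion as an estimate with a confidence interval rather than as a powered test.

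Cost: one sentence, one model term, and a less favourable stated figure. No extra patients, sites or follow-up.
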